#### Quality of life (QoL)

Endometriosis-related QoL will be assessed using the French version of the Endometriosis Health Profile-30 + 23 (EHP-30+23) [39]. The main questionnaire (30 items) is complemented by a 23-item facultative questionnaire with six subscales (treatment, relationship with children, work life, sexual intercourse, medical profession, and infertility). Items are rated on a Likert scale ranging from 0 (never) to 5 (always). A score ranging from 0 to 100 is calculated, with the low the score the better the QoL. The short version (EHP-5) will also be proposed in order to compare its accuracy to the long version.

### Secondary outcome measures

Except for pain, fatigue, and PA which will be assessed at the same points of measurement as the primary outcomes, all secondary outcomes will be assessed at baseline, at the end of the study (6 months), and at 6 months follow-up.

Pain and fatigue will be assessed, separately, using visual analog scales from 0 (no pain or no fatigue) to 10 (pain or fatigue as extreme as possible) [40, 41]. The questions will be about the current pain or fatigue, the pain or fatigue during the last 7 days, and the pain or fatigue during endometriosis crisis. A decrease of 1 point on VAS will be considered as significant [19]^1^.

PA will be assessed using the International Physical Activity Questionnaire (IPAQ, [42]). The IPAQ measures the number of days per week and the time (hours and minutes) spent in vigorous, moderate PA and in walking during past 7 days. The questionnaire also includes questions about time spent in sedentary behaviors. This primary outcome will be defined as the proportion of patients who achieve the internationally recommended level of PA international recommendations, i.e., at least 150 min per week of moderate to vigorous PA [43].

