**Methods:**

This multicentric randomized-controlled trial will propose to 200 patients with endometriosis to be part of a trial which includes a 6-month program with 45 min to more than 120 min a week of adapted physical activity and/or 12 sessions of endometriosis-based education program. Effects of the program will be compared to a control group in which patients will be placed on a waiting list. All participants will be followed up 3 and 6 months after the intervention. None of the participants will be blind to the allocated trial arm. The primary outcome measure will be quality of life. Secondary outcomes will include endometriosis-related perceived pain, fatigue, physical activity, and also self-image, stereotypes, motivational variables, perceived support, kinesiophobia, basic psychological need related to physical activity, and physical activity barriers. General linear models and multilevel models will be performed. Predictor, moderator, and mediator variables will be investigated.

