### Description of the “APA” arm

In addition to PA recommendations, participants randomized to this arm will receive PA sessions via videoconference for 6 months. The sessions will be based on the personalized PA assessment and will last between 45 min (at the beginning of the program) and 1 h, 1 to 3 times a week, supervised or on their own. Participants will benefit from this program free of charge (Table 1).

**Table 1 Tab1:** Duration and type of PA proposed

Physical activity	Month #1	Month #2	Month #3	Month #4	Month #5	Month #6
Pilates/stretching/yoga Intensity: light to moderate *Sessions with APA teacher*	45 min	45 min	60 min	60 min	60 min	60 min
Cardio fitness Intensity: light *Sessions with APA teacher*			60 min	60 min		
Cardio Intensity: light to moderate *Sessions with APA teacher*					60 min	60 min
Pilates/stretching/yoga + cardio fitness Intensity: light to moderate *Autonomous sessions*				Duration decided by participants		
Total duration of PA from the study	45 min	45 min	120 min	> 120 min	> 120 min	> 120 min

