### Assessment of PA level at inclusion

The PA tests carried out at inclusion will allow the evaluation of the level (beginner, intermediate, expert) of the participants in aerobic activity, mobility, balance, and flexibility.

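### The physical-activity outcome is stated only as reaching 150 min/week or not, so real gains below that line go uncounted; baseline-adjusted IPAQ minutes on a log or rank scale should be the stated measure

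*Protocol article*

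**What the plan says.** Under Secondary outcome measures, PA is measured with the IPAQ, which records days per week and "time (hours and minutes) spent in vigorous, moderate PA and in walking during past 7 days". That information is then reduced to one yes/no result per patient: "This primary outcome will be defined as the proportion of patients who achieve the internationally recommended level of PA", which is spelled out as "i.e., at least 150 min per week of moderate to vigorous PA". The article states no other PA score. (The word primary in that sentence is a separate labelling slip; the outcome is listed among the secondary ones.) PA is measured at all five time points: "Except for pain, fatigue, and PA which will be assessed at the same points of measurement as the primary outcomes".

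The abstract gives the programme as "45 min to more than 120 min a week of adapted physical activity". Table 1, in the description of the APA arm, splits this into supervised sessions of light or light-to-moderate intensity. From month 4 it adds autonomous sessions whose length the participants choose. One Table 1 row, supervised in months 3 and 4, reads "Cardio fitness Intensity: light". The text under Program structure describes all sessions as low to moderate, and the text under Structured sessions gives the cardio fitness sessions as light to moderate.

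**The concern.** A threshold counts only patients who cross it. The supervised part of the programme lies below this one, and some or all of its minutes may be too light to count. A patient who moves from 0 to 120 min/week is scored as not achieving; one who moves from 145 to 155 is scored as achieving.

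This matters because raising PA is part of the first trial objective. The Discussion also expects the APA and education arms to be equivalent on quality of life, pain and fatigue, but expects APA to raise PA during and after the intervention. PA is thus the outcome on which those two arms are predicted to differ. The Background describes these patients as practising little PA or avoiding it, so gains that end below 150 min are a plausible form of benefit, and the stated outcome cannot register them.

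**Working it through.** **Step 1: reproduce Table 1.** Inputs are the supervised rows, read as minutes per week (the abstract supplies the unit).

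| Month | 1 | 2 | 3 | 4 | 5 | 6 |
|---|---|---|---|---|---|---|
| Pilates/stretching/yoga, light to moderate | 45 | 45 | 60 | 60 | 60 | 60 |
| Cardio fitness, light | – | – | 60 | 60 | – | – |
| Cardio, light to moderate | – | – | – | – | 60 | 60 |
| Supervised sum | 45 | 45 | 120 | 120 | 120 | 120 |
| Total stated in Table 1 | 45 | 45 | 120 | >120 | >120 | >120 |

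The sums match; the > sign reflects the open-ended autonomous sessions.

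**Step 2: compare with 150.** Count every light-to-moderate minute as moderate, which is the most favourable reading.

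| Month | 1 | 2 | 3 | 4 | 5 | 6 |
|---|---|---|---|---|---|---|
| Ceiling by Table 1 labels | 45 | 45 | 60 | 60 | 120 | 120 |
| Shortfall to 150 | 105 | 105 | 90 | 90 | 30 | 30 |
| Ceiling by Program structure and Structured sessions | 45 | 45 | 120 | 120 | 120 | 120 |
| Shortfall to 150 | 105 | 105 | 30 | 30 | 30 | 30 |

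At 3 months the supervised ceiling is 60/150 = 40% of the threshold by Table 1, or 120/150 = 80% by the text. At 6 months it is 80% on both. If only half of the light-to-moderate time is moderate, the 6-month ceiling is 60 min and the shortfall 90.

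**Step 3: a case that can be checked by hand.** Assumptions, none from the article: other moderate-to-vigorous activity is normal with mean 90 and SD 80 min/week, there are 50 per arm (200/4), and the gain is 60 min (half of 120).
- Control proportion: 1 − Φ((150 − 90)/80) = 1 − Φ(0.75) = 0.23.
- Treated proportion: 1 − Φ((150 − 150)/80) = 0.50. Half of the treated patients still score as not achieving.
- Power for the proportions, two-sided 0.05: 0.82.
- Power for mean minutes: the standard error is 80 × √(2/50) = 16, and 60/16 = 3.75. Φ(3.75 − 1.96) = 0.96.

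Over means of 60-120, power is 0.75-0.84 against 0.96 for a gain of 60, and 0.24-0.31 against 0.47 for a gain of 30.

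**Step 4: skewed minutes, by simulation.** Assumptions: log-normal minutes, median 60, 90 or 120, log-SD 0.9, baseline to follow-up correlation 0.6. Arm sizes are 50, or 50 × 0.8 = 40 after the 20% dropout that the article allows for.

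| Gain per treated patient | Power, proportion at 150 | Power, baseline-adjusted log or rank minutes |
|---|---|---|
| 40 or 60 min, 40 per arm | 19-53% | 69-100% (log) |
| 40 or 60 min, 50 per arm | 22-63% | 79-100% (log) |
| 40-60 min, also allowing 25% zero-minute patients and uneven gains | 18-69% | 44-100% |
| 90 min | 68-99% | higher than the proportion |

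The ranges overlap across scenarios, but within each scenario the log or rank analysis has more power. With a constant gain of 40-60 min, 15-41% of patients are at or above 150 at baseline, and 38-75% of treated patients still score as not achieving.

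Untransformed minutes are not a safe substitute on skewed data. At 40 per arm, median 120 and gain 60, baseline-adjusted raw minutes have power 0.42 against 0.54 for the proportion. At medians 90-120 and gain 90 the figures are 0.70-0.87 against 0.95-0.97.

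**The case against.** The case for leaving the outcome alone has real substance. The 150-min level is a cited international recommendation and easy to explain. The IPAQ counts all activity in the past week, so autonomous sessions, up to three sessions a week in all, and activity outside the programme can carry a patient past 150. At 6 months 30 further minutes could be enough. PA is also measured 3 and 6 months after the programme, when the supervised dose no longer matters. The IPAQ minutes are collected in any case, and a statistical analysis plan that is not shown may use them. All of this stands, and it limits the point to how the article defines a secondary outcome.

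It also rules out four stronger readings that a reader might infer:
- **Patients already at 150 cannot be successes.** Not supported. The outcome is the proportion who achieve the level, not conversion from below it. Such patients count as achieving in either arm if they stay there; they merely add little to the contrast. That the inclusion tests "will allow the evaluation of the level (beginner, intermediate, expert) of the participants" does not show how many there are, because those grades describe aerobic activity, mobility, balance and flexibility, not weekly minutes.
- **The ceiling at 3 months is 40%.** Not established. It rests on one Table 1 label; the text under Program structure and Structured sessions gives 80%.
- **The outcome will show no effect although everyone follows the programme.** Not supported. Failure to reach 150 is possible, not certain, and with gains of 90 min the proportion has 68-99% power.
- **Programme minutes should be subtracted.** The section on autonomous sessions says only that they can be declared, so the subtraction would be incomplete.

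**Conclusion.** The point holds in limited form. As stated, the PA outcome discards minutes that are already collected and can score a full attender with a substantial gain as not achieving. The comparison of 120 supervised minutes with 150 comes from the article's own figures. The power loss does not: it rests on assumed distributions and gains. For gains of 40-60 min it is about 18-69% for the proportion against about 44-100% for log or rank minutes. For gains of 90 min or more the practical difference is small. The direction is the same in every scenario examined for the log and rank scales, but not for untransformed minutes.

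The differing intensity labels for the month 3-4 cardio fitness sessions are an inconsistency within the article. The quality-of-life primary outcome is unaffected, and nothing here implies a change to the exercise programme.

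**What to change.** Under Secondary outcome measures, define the PA outcome as weekly minutes of moderate-to-vigorous PA from the IPAQ, analysed on a prespecified log(minutes + 1) or rank scale and adjusted for baseline minutes. Choose the scale before any data are seen. Keep the proportion reaching 150 min/week as a supportive result, shown separately for patients below 150 and at or above 150 at baseline. Reconcile the intensity given for cardio fitness in Table 1 with that under Program structure and Structured sessions, so that readers know which supervised minutes could count at 3 months.

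The cost is wording in the outcome section and the analysis plan. No new data are needed, and the planned general linear and multilevel models suit a continuous score. The drawback is that a transformed measure is harder to communicate, which is why the proportion stays beside it. The change does not credit light sessions, since these remain outside moderate-to-vigorous PA under either definition.

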#### Motivational variables

From the theory of planned behaviors (TPB) [44], intention (three items), attitudes (six items), norms (six items), and perceived behavioral control (eight items) will be assessed within 7-point scales [45].

From self-determination theory [36], motivation for PA will be assessed using EMAPS (motivation toward PA un health context scale [Echelle de Motivation envers l’Activité Physique en contexte de Santé] [46]). The 18 items are assessed within a 7-point Likert scale from 1 (does not correspond at all) to 7 (corresponds very strongly). The types of motivation evaluated are intrinsic, integrated, identified, introjected, external regulation, and amotivation.

Basic psychological needs will be also assessed. Twenty-nine items will allow to measure satisfaction, frustration, and unfulfillment of the need for autonomy, competence, and relatedness within a 7-point Likert scale from 1 (strongly disagree) to 7 (strongly agree) [47].

#### Barriers to PA

This questionnaire will evaluate perceived barriers to PA related to health (7 items), beliefs (7 items), environment (10 items), and safety (6 items) within a 5-point Likert scale form 1 (not important) to 5 (important) [48].

#### Kinesiophobia (Tampa)

The fear of being hurt during physical practice will be assessed using 17 items and a 4-point Likert scale from 1 (strongly disagree) to 4 (strongly agree) [49].

#### Stereotype

The questionnaire was adapted from a study on cancer, and PA stereotypes will measure the perception of the ability to endometriosis patients to practice PA within 19 items using a 6-point Likert scale from 1 (not agree at all) to 6 (totally agree) [50].

#### Social support

Social support from friends (12 items), life partner (if relevant, 12 items), and family (15 items) will be assessed within 16 to 39 items using a 5-point Likert scale from 1 (never) to 5 (very often) [51–53].

#### Self-concept

Self-concept about health (8 items), adiposity (6 items), sport skills (6 items), physical appearance (6 items), global physical satisfaction (6 items), and global self-esteem (8 items) will be measured using 5-point Likert scale from 1 (wrong) to 5 (true) [54].

#### Functional capacities

Physical assessment consisted of 2 minutes knee raise test (cardiorespiratory endurance), the Unipedal Stance Test (UPST) (balance and proprioception), Back Scratch Test (high flexibility), 30 s Chair Stand Test (explosive strength of lower limbs), and Sit and Reach (low flexibility).

### Participant timeline {13}

Participant timeline and checkpoints are summarized in Fig. 2.

**Fig. 2 Fig2:**
[figure not shown]
Participant timeline. TPB, theory of planned behaviors; QoL, quality of life

### Sample size {14}

Two hundred participants will be recruited. This sample size was chosen for several reasons: lack of article on the topic and resource limitations [55]. Except for one, all previous studies recruited or planned to recruit a sample size below 200. Furthermore, the specialists working on the project receive between 5 and 30 endometriosis patients per week. By taking the smallest number of patients and considering the possibility that these patients may refuse to participate or fall into the exclusion criteria, we can assume that only 2 women per week will be included in the study (*N* = 2 × 7 hospitals × 20 weeks of recruitment = 280). Of these participants, 20% may drop out of the study (*N* = 224). We performed sensitivity analyses for repeated measures ANOVA analysis. Effect sizes found were small to medium (*N* = 200 to be more conservative, *α* = 0.05, *β* = 0.90).

### Recruitment {15}

Participants will be recruited online via social media, printed media, radio, and patient associations as well as through the endometriosis specialists who are part of the study. Patients will receive a flyer, and those interested in participating will receive a link, QR code, and the email address of the principal investigator to be able to demonstrate his/her interest.

## Assignment of interventions: allocation

### Sequence generation {16a}

Participants will be randomized to one of the four arms using complete randomization which consist of uniformly distributing them. This procedure is performed using an R script. We opted for this procedure to avoid selection bias as this is the only procedure that does not permit to guess the assignment (Supplementary Material). Moreover, it minimizes various bias and various methods allows to correct the bias provoked by unbalanced in arms [56].

### Concealment mechanism {16b}

Each participant will be entered in the database to be allocated only once the consent form and the baseline online questionnaire are completed and sent to the principal investigator. Thus, each participant will be included chronologically, the date and hour of the last document sent in the principal investigator’s mailbox being the references. The principal investigator is the only one to know when the document was received. Allocation concealment will be ensured as R script will not release the randomization code until the patient has been included into the trial.

### Implementation {16c}

Randomization will be implemented by the principal investigator. Participants will receive an email to inform them about their allocation.

## Assignment of interventions: blinding

### Who will be blinded {17a}

Regarding the design of the intervention, researchers and participants will not be blinded to the allocated trial arm.

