### Intervention description {11a}

All participants in the study will receive a personalized PA assessment (physical tests) after inclusion, before the start of the program. This assessment will be conducted by an APA teacher. A booklet on PA recommendations, in particular the health benefits of PA and the latest studies on PA and endometriosis, will be given to all participants. This booklet will also include a link to a video of movements to perform. Participants will receive a second PA assessment at 6 months (end of the intervention).

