### Initial contact

After the assessment by the APA teacher and before the start of the program, the APA teacher will explain to the participants how the videoconference platform works. He/she will then present the personalized APA program to them.

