### Procedure for unblinding if needed {17b}

As the design is open label, unblinding will not occur.

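### The reason given for not blinding does not extend to whoever scores the month-6 functional tests, so an APA teacher may test the participants she trained: a risk of arm-dependent detection bias in one secondary outcome

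*Protocol article*

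**What the plan says.** Who will be blinded {17a} reads: "Regarding the design of the intervention, researchers and participants will not be blinded to the allocated trial arm". The next section, Procedure for unblinding {17b}, adds: "As the design is open label, unblinding will not occur". The design of the intervention is the only reason given, and no blinded role is named anywhere in the article.

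Functional capacities, under the secondary outcome measures, lists five performance tests. It begins: "Physical assessment consisted of 2 minutes knee raise test (cardiorespiratory endurance), the Unipedal Stance Test (UPST) (balance and proprioception", and goes on to the Back Scratch, 30 s Chair Stand and Sit and Reach tests.

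Intervention description {11a} applies the tests to all four arms: "All participants in the study will receive a personalized PA assessment (physical tests) after inclusion, before the start of the program". It then names the tester: "This assessment will be conducted by an APA teacher". The repeat is stated separately, without a tester: "Participants will receive a second PA assessment at 6 months (end of the intervention".

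Initial contact, within the description of the APA arm, links testing to delivery: "After the assessment by the APA teacher and before the start of the program, the APA teacher will explain" the videoconference platform, and then presents the personalised programme.

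**The concern.** An unblinded participant who fills in a questionnaire is a limitation that this trial cannot design away. An unblinded tester is different, because the tester's knowledge of the arm is a choice.

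The functional tests are the only outcome in the Outcomes section that is not self-reported. Knee raises and chair stands are counted, balance is timed and reach is measured, and all of them respond to how hard the participant is urged on. If the tester is the teacher who has worked with her for 6 months, both the encouragement and the scoring may be more generous than for a participant whom the tester hardly knows.

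A leniency common to all arms would cancel in the comparison. This one would not, because only the two APA arms contain participants with a trainer. A difference between an APA arm and a non-APA arm could then appear without any true effect on function.

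**Working it through.** The protocol reports no figure on this point, so there is nothing to reproduce. The main check is to read the sections together.

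1. **Scope of the reason.** {17a} rests on the design of the intervention. That covers participants, who know what they receive, and those who deliver the sessions. It also fits the principal investigator, who randomises ({16c}) and takes part in education sessions (description of the education arm). It does not cover a person whose only task is to score a test at month 6.
2. **Who tests.** {11a} assigns the first assessment to an APA teacher. The month-6 assessor is not named, and no independence from delivery is required.
3. **Who delivers.** Initial contact and the APA program section give delivery to the APA teacher. Tester and deliverer are therefore the same role, though not necessarily the same person.
4. **Why the role matters.** Strategies to improve adherence {11c} gives APA teachers a notebook of motivational strategies, so encouragement is part of their work. The same section recognises that results may depend on the teacher, but deals with this only for the sessions and not for the testing.
5. **Whether exposure differs by arm.** In the APA and APA + education arms the month-6 tester may be the participant's own trainer. In the education and waitlist arms no such relationship exists before month 6.

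**Illustration of size.** The document gives no scoring shift, so b is an assumption.

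- Inputs: N = 200 (Sample size {14}) and allocation 1:1:1:1 (Trial design {8}), so n = 200/4 = 50 per arm; two-sided 5% test ({20a}), critical value 1.96.
- Assumption: no true effect, and a shift of b SD in favour of one arm.
- Standard error of the difference in SD units: SE = √(2/n) = √(2/50) = 0.20.
- False-positive rate = Φ(b/SE − 1.96) + Φ(−b/SE − 1.96).

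| Assumed shift b (SD) | b/SE | False-positive rate |
|---|---|---|
| 0 | 0 | 0.050 |
| 0.1 | 0.5 | 0.079 |
| 0.2 | 1.0 | 0.170 |
| 0.3 | 1.5 | 0.323 |

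The table shows how sensitive a comparison of two arms is to a modest shift. It does not estimate the shift in this trial.

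**The case against.** The strongest reply is that the mechanism is inferred from silence. The sentence naming an APA teacher concerns the first assessment. Initial contact describes onboarding and does not say that the same teacher later leads the sessions. A condensed article may leave the testing roster to the full protocol. This stands in part: a reader might infer that the trainer will score the month-6 tests, or that the bias is built into the outcome, and the document supports neither. What remains is that {17a} makes a positive statement about blinding, gives a reason that does not reach the tester, and leaves in place an arrangement in which exposure differs by arm.

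A reader might also take {17a} to deny blinding to everyone. It names researchers and participants. That no tester is blinded follows only from the open-label description together with the absence of any blinded role.

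The importance can be overstated too. The tests do not appear among the secondary outcomes in the abstract, in the objectives {7} or in the data collection plan {18a}. At baseline they also serve to set the participant's level and to personalise her sessions. The protocol gives them no role in corroborating the questionnaires. All of this is correct and limits the weight of the point, but the tests are still listed as an outcome.

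The tester's control over the clock is limited. Two tests have fixed durations, two measure flexibility, and only the one-leg stance ends when the clock is stopped. Encouragement and the judgement of what counts remain.

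Finally, larger or smaller groups might be used to vary the illustration. Pooling the two APA arms against the other two is foreseen in {20b} only if 200 participants cannot be reached, so a pooled comparison at the full 200 is not planned. Taking the 20% dropout off 200 is only one reading of {14}, which applies it to 280, obtains 224 and then works with 200. The illustration therefore stays at 50 per arm.

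**Conclusion.** The concern holds as a risk of detection bias confined to the month-6 functional tests. The stated reason for open-label conduct does not justify leaving the tester unmasked, and nothing in the article separates testing from training.

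It does not extend further. The primary outcome (EHP-30+23), pain, fatigue, IPAQ and the other questionnaires are reported by unblinded participants, and a masked tester would not change that.

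The size is unknown. The error rates of about 8%, 17% and 32% rest wholly on assumed shifts of 0.1, 0.2 and 0.3 SD, 50 analysed per arm, a comparison of two arms and no true effect. The point merits a change because the remedy is cheap, but it does not threaten the trial's main conclusion.

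**What to change.** Keep the statement in {17a} that researchers and participants are unblinded. It is a true disclosure and should not be narrowed. Add to {17a} and {11a} that:

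- the month-6 functional tests are run by one of the trial's existing APA teachers who has not taught that participant and is not told her arm;
- one fixed script governs instructions and encouragement for every participant;
- participants are asked not to disclose their arm to the tester.

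The article refers to APA teachers in the plural ({11c} and {22}), so exchanging participants among teachers for one assessment needs no new role. The costs are some scheduling effort and occasional unmasking when a participant mentions her arm. The number of teachers is not given. If there are few, a teacher may know who attends the APA groups and masking will be incomplete. In that case the minimum is a tester who did not train the participant, with the remaining limitation stated in the report.
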